#### Health-related quality of life

The EuroQol EQ-5D instrument will be used to measure health-related quality of life, expressed as utility values ranging from 0 to 1, where 1 represents perfect health[49]. The utility weights captured by these preferences will enable the derivation of the Quality Adjusted Life Years (QALY) for each intervention and will be used in cost-utility analyses. One advantage of using this instrument is that results of this study can be compared with those of a previous trial which compared corticosteroid injection, physiotherapy and a wait and see policy for LE [17].

#### Costs

Cost data will be collected from a societal perspective, meaning that an attempt to capture all of the costs, regardless of which party or parties incur them, will be made. It will include a) direct health care costs, such as visits to doctors, therapists, investigations and prescribed medication; b) direct non-health care costs, such as costs of over-the-counter medication, hours of paid and unpaid household help, transportation and other out-of-pocket expenses; c) indirect costs, such as absence from work, housekeeping and other daily activities [50]. Participants will be asked to recall their out-of-pocket expenses incurred over the preceding month during a structured telephone interview by a research assistant not involved in outcome measurement. The initial interview date will be randomised by a computer-generated number sequence to 4, 8 or 12 weeks following commencement of the study and then subsequent interviews performed at three monthly intervals. This method of sampling was chosen to provide sufficient information while minimising the time commitment required of participants [51]. In addition, participants will be asked to provide consent for their Medicare data on in-hospital, out-of-hospital and pharmaceutical services to be provided by Medicare Australia. These data will capture expenditures incurred under Australia's universal, compulsory health care financing scheme, Medicare. This includes all expenditures incurred for general practitioner and specialist services, as well as pharmaceuticals that are listed on the Pharmaceutical Benefits Scheme.

#### Willingness-to-pay

A contingent valuation study will be conducted to elicit an individual's willingness-to-pay (WTP) for relief of the symptoms of LE. The contingent valuation approach results in monetary valuation of the benefits produced by a health program or health state [52]. An advantage of this approach is it allows valuation of transitory health states, which may be important given previous trials suggest considerable temporal variance in the effectiveness of interventions for LE [10]. Participants will be questioned at baseline assessment regarding the greatest amount they are willing to pay, based on the following hypothetical scenario: "*Suppose that your current elbow pain will persist over the next 12 months if untreated. Imagine that there is a new treatment that is quick and non-invasive. If it works, it will provide an immediate and complete cure of your tennis elbow. However, this treatment only works on 1 in 2 people. The treatment is not covered by Medicare or private insurance*." Bias will be minimised by using both a bidding game approach and a binary response approach. The bidding game approach involves exposing respondents to repeated bids and identifying the point of indifference between those bids. In the binary response approach, the respondent is asked to respond to only one bid. In both approaches, four bids ($50, $650, $1250 and $1850 in Australian Dollars) will be randomly allocated to respondents. The randomisation of bids is a further measure to reduce the bias that may be generated by the choice of a starting bid [53]. Specifically, it is known that high (low) starting bids may lead to higher (lower) WTP valuations. The starting bids will be based on the mean ± 2 standard deviations derived from a similarly designed pilot study of WTP in LE participants.

#### Adverse events

All adverse events, defined as any negative or unwanted reactions to intervention, will be recorded. These will include pain (lasting longer than 7 days), skin pigmentation changes, subcutaneous atrophy or any other reported physical discomfort. As well as the adverse effects committee (chaired by BV) that will manage adverse reactions at the time of the adverse reaction, we will administer a questionnaire at 8 and 52 weeks to record all such patient identified events. This will capture additional ill effects not reported at the time of their occurrence. These are likely to be minor aggravations in symptoms. The questionnaire will use open-ended questions and will be placed in a sealed envelope to be opened by a research assistant not involved in outcome measurement. The intervention-specific incidence of each adverse event will be computed.

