**Methods:**

A randomised placebo-controlled clinical trial with a 2 × 2 factorial design will evaluate the clinical efficacy, cost-effectiveness and recurrence rates of adding physiotherapy to an injection. In addition, the clinical efficacy and adverse effects of corticosteroid injection beyond that of a placebo saline injection will be studied. 132 participants with a diagnosis of lateral epicondylalgia will be randomly assigned by concealed allocation to one of four treatment groups – corticosteroid injection, saline injection, corticosteroid injection with physiotherapy or saline injection with physiotherapy. Physiotherapy will comprise 8 sessions of elbow manipulation and exercise over an 8 week period. Blinded follow-up assessments will be conducted at baseline, 4, 8, 12, 26 and 52 weeks after randomisation. The primary outcome will be a participant rating of global improvement, from which measures of success and recurrence will be derived. Analyses will be conducted on an intention-to-treat basis using linear mixed and logistic regression models. Healthcare costs will be collected from a societal perspective, and along with willingness-to-pay and quality of life data will facilitate cost-effectiveness and cost-benefit analyses.

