### Injection

A routine clinical examination will be conducted by the treating medical practitioner prior to injection of either (1) 1 ml Triamcinolone Acetonide (10 mg/ml) (Kenacort-A 10) with 1 ml Lignocaine (1%) [Corticosteroid injection] or (2) 0.5 ml Isotonic Saline (0.9%) [Saline injection]. Injection will be administered into the most palpably tender point(s) in the region of the lateral epicondyle, consistent with previous studies [10,16,19,20]. The syringe will be drawn up and administered with the participant unable to view its contents to facilitate participant blinding. In addition, standardised post-injection information will be provided verbally and in the form of a printed pamphlet based on published recommendations [10,16,21]. Rest from all strenuous activity for 1–2 weeks following injection will be strongly recommended, followed by gradual return to normal activities. Participants will be instructed to avoid aggressive return to activities even if substantial relief is obtained, to minimise potential recurrence of their symptoms. All participants will be warned of normal post-injection responses and to inform their doctor if there is any suggestion of infection or other adverse events. All adverse reactions will be managed by a committee chaired by the chief investigator (BV).

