This study adheres to the CONSORT statement for randomised controlled trials [57,60]. Randomisation of participants by concealed allocation will be performed, as this feature is known to minimise bias [61]. Blinding strategies will be employed such that the participant and assessor are blind to the injection content (double blinding). The nature of the physiotherapy program means that blinding of patients and practitioners is not possible, however the assessor will be blinded to the allocation of physiotherapy (single blinding). Success in blinding of injection content will be evaluated at 8 and 52 weeks by both participant and assessor. This trial uses outcome measures that have established reliability and validity to enhance the quality of the outcomes and facilitate comparison with studies of LE and other musculoskeletal conditions. The statistical analysis will be conducted on an intention-to-treat basis. The influence of group allocation on the utilisation of not-per-protocol treatments will also be evaluated, in order to fully describe patient behaviours in a realistic context in which there are more than the study's interventions available. This study has been designed to optimise applicability to the clinical setting so that practitioners will be able to use the data in their day-to-day management of LE. For example, participants will be included on explicit clinical diagnostic criteria, interventions will be delivered in primary care settings and many of the outcome measures can be readily used in clinical practice.

It is becoming increasingly important to determine the costs relative to the benefits, measured either in monetary values or gains in health-related quality of life, of the combined injection and physiotherapy approach. The inclusion of an economic evaluation in this trial provides a basis for considering the economic arguments for investments in the interventions of interest here, and their comparison to other health sector interventions. The measurement of costs from a societal perspective encompasses those costs incurred by the patient and his/her family, private and public sector payments and productivity losses [53]. Evaluation of the value of improved health will be measured using physical measures of health-related quality of life (e.g., QALYs) and WTP measures. The range of measures that will be used in this study provides us with considerable flexibility to examine the economic impacts of the interventions.

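### Adverse events count only if attributed to treatment, and the planned incidence does not say whether it is tallied by randomised group or by the treatment blamed

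*Protocol article*

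**What the plan says.** The definition is in the Adverse events section of the Protocol article: "All adverse events, defined as any negative or unwanted reactions to intervention, will be recorded". Examples follow: "These will include pain (lasting longer than 7 days), skin pigmentation changes, subcutaneous atrophy or any other reported physical discomfort". Collection has two routes. Reactions are dealt with by a committee as they arise, and in addition "we will administer a questionnaire at 8 and 52 weeks to record all such patient identified events". The questionnaire is open-ended and sealed, and is opened by a research assistant who takes no part in outcome measurement. The only summary given is "The intervention-specific incidence of each adverse event will be computed".

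The aim that this must serve is in the Abstract (Methods): "adverse effects of corticosteroid injection beyond that of a placebo saline injection will be studied". On blinding, the Discussion says that the participant and the outcome assessor do not know what was injected. It concedes that patients and practitioners cannot be blinded to physiotherapy, although the assessor is. Methods/design lists four groups, two with physiotherapy and two without.

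**The concern.** The definition describes an adverse reaction rather than an adverse event. Before prolonged pain or discomfort enters the count, it has to be seen as a consequence of treatment. The questionnaire carries the same restriction, because it records events of the kind just defined. The broad catch-all in the list of examples widens the type of event but still falls under that definition.

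A randomised trial does not need this filter, since comparing the arms shows which harms are due to treatment without anyone's opinion. With the filter in place, the count depends partly on what people believe about the treatment. That matters most where they know the treatment, which is the physiotherapy factor. The same section expects most late-reported events to be minor symptom aggravations, and these are hard to tell from the natural course of the condition.

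The wording of the summary adds a second difficulty. If the incidence is tallied by the treatment blamed, a participant who had no physiotherapy cannot have a physiotherapy reaction, so that incidence has nothing to be compared with. A later analysis plan could settle the table. It could not recover events that were never recorded because nobody blamed a treatment.

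**Working it through.** The documents give no adverse event rate, margin or power, so there is no figure of theirs to reproduce. The check sets the texts side by side and then illustrates the size with assumed rates.

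**1. What attribution can affect, by factor**

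- *Injection.* Participants are the source of the questionnaire data and do not know what was injected. Any tendency to blame the injection should be similar after steroid and saline, as far as blinding holds. The text does not say whether the injecting practitioner, the committee or the research assistant is blind to injection content.
- *Physiotherapy.* Patients and practitioners know the allocation. In the two combined groups an event has two candidate causes; in the injection-alone groups it has one.

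**2. What the two readings of the summary imply**

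Let b be the background event rate, equal in both halves, with no true harm from physiotherapy. Let a be the share of events blamed on physiotherapy among those who receive it.

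- Every event counted, by randomised group: expected difference = b − b = 0.
- Tally by treatment blamed: physiotherapy half = a × b; no-physiotherapy half = 0 by construction; apparent excess = a × b.
- Tally by randomised group with the causal definition kept: if a share c1 of events is called a reaction to some treatment in the combined groups and c0 in the injection-alone groups, the recorded difference is b × (c1 − c0). This is 0 only if c1 = c0. Reading the summary as by group therefore restores a comparator but does not remove the filter.

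**3. Illustration of the tally by treatment blamed**

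Inputs: 132 participants (Sample size section). Equal allocation is an assumption, giving 132 / 2 = 66 per half. The values of b and a are assumed. Expected participants with an event in the physiotherapy half = 66 × b × a.

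| | b = 5% | b = 10% | b = 20% | b = 30% |
|---|---|---|---|---|
| All events, each half (66 × b) | 3.3 | 6.6 | 13.2 | 19.8 |
| Blamed on physiotherapy, a = 25% | 0.8 | 1.7 | 3.3 | 5.0 |
| Blamed on physiotherapy, a = 50% | 1.7 | 3.3 | 6.6 | 9.9 |
| Blamed on physiotherapy, a = 100% | 3.3 | 6.6 | 13.2 | 19.8 |

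The comparator in the last three rows is 0 by construction. The apparent excess runs from 0.05 × 0.25 = 1.25 percentage points to 0.30 × 1.00 = 30 percentage points, although the true excess is 0.

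**The case against.** The strongest defence is that one loosely worded sentence is being read as an attribution system that the article does not describe. No causality adjudicator is named; the committee manages reactions and is not said to decide which ones count. The catch-all in the examples is inclusive. Table 2 schedules adverse events at follow-up for participants generally, so the groups without physiotherapy are observed too. The Clinical Efficacy section puts all analyses on an intention-to-treat basis, and the aim of measuring harm beyond saline can only be met by comparing arms. Both favour reading the summary as by randomised group. Pain, disability and global improvement are also measured in every arm, which gives symptom flares a randomised comparator outside the adverse event data.

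Much of this stands. The by-group reading is available and may be the intended one, and the efficacy outcomes give partial background on flares. What does not yield is the definition itself, because it acts at collection, before any table is drawn up.

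A reader might go further and infer that people who know the injection content decide which events count, so that the steroid versus saline harm comparison is itself distorted. The volumes differ (1 ml + 1 ml = 2 ml against 0.5 ml), so whoever injects may be able to tell them apart, and participants are told to report suspected adverse events to their doctor. But the documents do not support that inference. The participant is blind to content, the Injection section does not say who draws up the syringe, and nothing says that the doctor filters what is recorded. Nor do the documents give any basis for assuming that events are blamed more often after steroid than after saline.

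**Conclusion.** The point holds in a limited form. The definition builds attribution into the count, and the summary leaves open whose events are tallied against what. For steroid versus saline, participant blinding limits the bias; what remains is that the blinding of the injecting practitioner, the committee and the research assistant is not stated. For physiotherapy, attribution by people who know the allocation can distort the count. Under a tally by treatment blamed, the groups without physiotherapy supply a structural zero instead of a background rate.

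The range of about 1 to 30 percentage points shows how far attribution alone could move the physiotherapy figure. It is not an estimate for this trial: it rests on assumed background rates and blame shares, equal allocation, and that one reading of the summary. It would also be too strong to say that physiotherapy harm has no control rate. The design provides two groups without physiotherapy, and a by-group tally would use them. The change is worth making as an inexpensive improvement that serves the stated aim on harm.

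**What to change.** In the Adverse events section, replace the definition with: *an adverse event is any untoward event after randomisation, whatever its presumed cause, collected in the same way in all four groups.* Replace the closing sentence on incidence with: *the number of participants with each event will be reported by randomised arm, and compared for corticosteroid versus saline and for physiotherapy versus none as risk differences with 95% confidence intervals.* If a judged cause is recorded, keep it as a descriptive item that does not determine whether an event is counted, and have it completed by someone blind to injection content.

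The cost is two sentences and one table. The downside is that more minor, unrelated events will be recorded. No treatment or clinical procedure changes. The definition should be settled before collection starts, because the analysis cannot restore events that were left out.

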### Physiotherapy

A standardised physiotherapy treatment protocol has been devised based on a recently evaluated program [10]. Eight, 30 minute physiotherapy sessions will be provided by a post-graduate qualified physiotherapist over an 8 week period. The initial physiotherapy consultation will be scheduled prior to injection to allow baseline measurement and familiarisation with the program. The primary rationale for physiotherapy rehabilitation will be relief of pain, restoration of motor function and facilitation of tendon healing [22,23]. A pragmatic multimodal program comprising education, manipulation and therapeutic exercise will be used in conjunction with a home exercise program to address these aims.

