### Outcome assessment

Participants will be evaluated by a blinded assessor at baseline, 4, 8, 12, 26 and 52 weeks following randomisation. The 4 and 8 week time points will be used primarily to investigate the short term effects of corticosteroid injection compared to saline injection and of addition of physiotherapy to injection respectively. The 52 week time point will provide a primary end point for study of all long term effects. The data from the other measurement points (12–52 weeks) will be used to derive indices for recurrence rates. These time points have been chosen on the basis of a previous study which noted deterioration in the corticosteroid injected group during this time period [10].

Socio-demographic information will be collected at baseline including age, gender, employment nature, smoking status, body mass index and physical activity status. Information will be sought regarding the nature, duration and onset of LE symptoms, previous treatment and presence of concomitant neck or arm pain. The following outcome measures will be collected at baseline assessment and at follow-up evaluations as outlined in Table 2.

**Table 2 T2:** Outcome measures used at baseline and follow-up interviews

**Outcome Measures**	**Time Point (weeks)**	
	
	**0**	**4, 8, 12, 26 & 52**
Global Perceived		x
Improvement		
Resting/Worst Pain (VAS)	x	x
Pain/Disability (PRTEE)	x	x
Quality of Life (EuroQol)	x	x
Anxiety/Depression (HADS)	x	
Kinesiophobia (Tampa)	x	
Pain-free Grip Force	x	x
Pressure Pain Threshold	x	x
Adverse events		x
Willingness-to-pay	x	
Costs		4 randomly allocated time points

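### Table 2 schedules adverse events at all five follow-ups, but the only solicited instrument described, a sealed questionnaire, is given at 8 and 52 weeks only

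*Protocol article*

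**What the plan says.** Two parts of the protocol article set the timing of adverse-event collection.

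- **Outcome assessment and Table 2.** The text states: "The following outcome measures will be collected at baseline assessment and at follow-up evaluations as outlined in Table 2". In Table 2 the row "Adverse events" is marked in the single follow-up column for weeks 4, 8, 12, 26 and 52.
- **Adverse events.** The scope is broad: "All adverse events, defined as any negative or unwanted reactions to intervention, will be recorded". On the instrument: "we will administer a questionnaire at 8 and 52 weeks to record all such patient identified events". It uses open-ended questions, is sealed in an envelope and is opened by a research assistant who takes no part in outcome measurement. It adds to reports made when events happen: "This will capture additional ill effects not reported at the time of their occurrence". The planned summary is: "The intervention-specific incidence of each adverse event will be computed".

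Three other statements bear on the point.

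- **Injection.** Every arm is injected, and the section says: "All participants will be warned of normal post-injection responses and to inform their doctor if there is any suggestion of infection or other adverse events".
- **Physiotherapy.** For the two physiotherapy arms: "Eight, 30 minute physiotherapy sessions will be provided by a post-graduate qualified physiotherapist over an 8 week period". The first consultation is placed before the injection.
- **Abstract, Methods.** Adverse effects of corticosteroid compared with saline injection are named as something the trial will study.

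**The concern.** The two schedules differ, and the text does not say which one staff should follow. If Table 2 governs, adverse events are collected at weeks 4, 12 and 26 by a method that is not described. If the Adverse events section governs, nothing is solicited at those visits.

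Two things are at stake. The first is blinding. All follow-ups are done by a blinded assessor, and the Discussion requires that assessor to stay blind to injection content. Skin pigment change and subcutaneous atrophy are among the named events and could hint at that content. The sealed envelope guards against this at weeks 8 and 52, but no equivalent is described for the other three visits.

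The second is completeness. Under the text, participants are asked about adverse events at week 8 and not again until week 52. An event that arises and settles in between is counted only if the participant volunteers it or recalls it at one year.

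There is also a lesser question. Participants given physiotherapy meet a practitioner more often, so they have more chances to mention an event. If such reports enter the incidence by intervention, the comparison of physiotherapy with no physiotherapy could be affected.

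**Working it through.** The document gives no adverse-event rate or capture rate, so there is no stated figure to reproduce. The check compares the schedules and then illustrates ascertainment on assumed inputs.

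**1. Schedules side by side**

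| Week | Marked in Table 2 | Sealed questionnaire in text |
|---|---|---|
| 4 | yes | no |
| 8 | yes | yes |
| 12 | yes | no |
| 26 | yes | no |
| 52 | yes | yes |

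Three of the five scheduled points have no described solicited method.

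**2. Interval between solicited collections**

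As written: 52 − 8 = 44 weeks. With the questionnaire at all five visits the longest interval is 52 − 26 = 26 weeks, and the others are 4, 4, 4 and 14 weeks.

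**3. Physiotherapy versus no physiotherapy (all inputs assumed)**

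Let p be the true incidence, equal in both; q the share of events captured by the routes open to everyone; and e the share of otherwise missed events picked up because of physiotherapy sessions.

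- Recorded without physiotherapy: p × q
- Recorded with physiotherapy: p × [q + (1 − q) × e]
- Spurious relative risk: 1 + (1 − q) × e / q, which does not depend on p

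| q | e = 0 | e = 0.25 | e = 0.75 |
|---|---|---|---|
| 0.6 | 1.00 | 1.17 | 1.50 |
| 0.8 | 1.00 | 1.06 | 1.19 |
| 0.9 | 1.00 | 1.03 | 1.08 |

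For example, with q = 0.6 and e = 0.75: 1 + 0.4 × 0.75 / 0.6 = 1.50. The document fixes neither q nor e, and e = 0 is compatible with it.

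**4. Corticosteroid versus saline (true incidence of 30% and 15% assumed, e = 0.5)**

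Each injection type is given with and without physiotherapy, so average capture is the same for both types.

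- q = 0.6: capture is 0.6 without and 0.6 + 0.4 × 0.5 = 0.8 with physiotherapy, mean 0.70. Recorded incidence is 0.30 × 0.70 = 0.210 and 0.15 × 0.70 = 0.105. The relative risk is 2.0, as in truth; the risk difference is 0.105 against a true 0.15.
- q = 0.8: capture is 0.8 and 0.9, mean 0.85. Recorded incidence is 0.255 and 0.1275. The relative risk is 2.0 and the risk difference 0.1275.

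For this comparison the effect is under-capture, which shrinks the absolute difference. It does not favour either injection.

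**The case against.** The strongest reply is that the mismatch is small and everything beyond it is inference. Much of that is right.

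- **Other collection exists.** A reader might infer that the questionnaire is the only collection shared by all arms. It is not: everyone is told to report adverse events to the doctor, and the questionnaire is presented as a supplement to those reports. The Recurrence section also plans interviews on symptom aggravation at 12, 26 and 52 weeks without restriction by arm, though these do not cover skin changes. So the documents do not show that delayed events rest wholly on 44 weeks of recall.
- **Tilt is not established.** A reader might infer that incidence will be inflated in the physiotherapy arms. Nowhere does the article say that events are asked about or recorded at physiotherapy sessions, and the week-8 questionnaire, which goes to all arms, covers the period of those sessions. Nor does it say how the reporting sources are combined.
- **The named comparison is protected.** A reader might infer that corticosteroid versus saline is biased by unequal contact. The factorial crossing balances that contact.
- **Table 2 may be shorthand.** One merged follow-up column could simplify the real schedule. Against this, costs have their own timing entry in the same table where they depart from the column, and adverse events do not.
- **A condensed article need not describe every form.** This is fair as to detail, but here two stated schedules disagree, which is different from an omission.

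What remains is the conflict itself, the undescribed method at three visits, and the long interval between solicited collections.

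**Conclusion.** The concern holds in limited form. The current text gives two schedules for adverse events, five time points against two, and for weeks 4, 12 and 26 it describes no method that keeps answers from the blinded assessor. On the text's schedule, 44 weeks separate the two solicited collections for an outcome tied to a stated aim.

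For corticosteroid versus saline the likely consequence is missed events and a smaller absolute difference, with the relative risk preserved if capture does not depend on injection type. For physiotherapy versus none, unequal ascertainment is a possibility of unknown size. The 1.00 to 1.50 range reflects assumed capture rates only and should not be quoted as an estimate. The efficacy sample size and analysis are not touched. The point should be corrected, but it does not undermine the design.

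**What to change.** 1. Reconcile the Adverse events section with Table 2 by giving the same sealed questionnaire, opened by the same kind of independent research assistant, at 4, 8, 12, 26 and 52 weeks. This settles the schedule, extends the existing blinding safeguard to every visit and cuts the longest interval from 44 to 26 weeks.
2. Keep all recorded events, from any route, in the overall incidence by intervention. Restricting it to questionnaire reports would drop events already told to the doctor, including suspected infection.
3. In addition, tabulate events by route (questionnaire or spontaneous), so that physiotherapy versus none can be checked on the solicited route common to all arms. For that check to be fair, the form should ask about all events since the last visit, whether or not already reported, and an event reported by both routes should count once in the overall incidence.

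The open-ended format can stay; prompted items would be a preference and are not needed to resolve the conflict.

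The cost is a short form at three visits that already take place, the handling of those envelopes, and one further table. Recorded event counts will probably rise somewhat, which should be noted when they are set against trials with less frequent questioning.
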